#### Body acupuncture (0.2 mm × 1.5 mm, DONGBANG Acupuncture Inc., Korea)

The following acupoints will be used: LI4 (HeGu), LI11 (QuChi), and LU9 (Tai Yuan) for the upper limbs (both); LR3 (Taichong), ST36 (ZuSanLi), and BL60 (KunLun) for the lower limbs; and GV20 (Bai Hui) and EX-HN-1 (Si Shen Cong) for the head. These acupoints were identified with reference to the Korean Medicine Convergence Research Information Center’s standard acupuncture database. Clinical and experimental studies on acupuncture treatment in CP have shown that LI4 (HeGu), LI11 (QuChi), and LU9 (Tai Yuan) can be used to improve upper limb stiffness and LR3 (Taichong), ST36 (ZuSanLi), and BL60 (KunLun) to improve lower limb rigidity. GV20 (Bai Hui) and EX-HN-1 (Si Shen Cong) can be used to improve cognitive function in CP [9–11].

Patients will receive acupuncture treatment in their most comfortable position (supine, lateral, or sitting position) without limiting their posture. A TKM doctor will conduct the acupuncture treatment at a depth of 1–5 mm without twisting and twirling manipulation. After 20 min, the TKM doctor will remove the needle and disinfect the area of the needle with alcohol. The patient will rest for 5 min after the acupuncture treatment.

#### Press needle (0.18 mm × 1.3 mm × 1.5 mm, DONGBANG Acupuncture Inc., Korea)

Patients with spastic CP will receive press needle treatment to reduce their muscle tone at the following acupoints: LI5 (Yangxi) and TE4 (Yangchi) for upper limb paralysis (affected side) and BL60 (Kunlun) and KI3 (Taisi) for lower limb paralysis (affected side). After applying the press needle, the practitioner will allow the patient to exercise the joint for 1 min and direct the patient to remove the press needle before washing hands and feet on returning home.

#### Herbal medicine

The herbal medicine used in this study is a combination of Yukgunza-tang and Yukmijihwang-tang extracts prepared by Kracie Pharma Korea Co. which is licensed by the Korea Food and Drug Administration and produced by a GMP-approved facility. The Yukgunza-tang extract contains the following raw materials (in an adult dose per day basis, 6 g): Ginseng Radix 4.0 g, Atractylodes Rhizoma Alba 4.0 g, Smilacis Rhizoma 4.0 g, Pinelliae Tuber 4.0 g, Fraxini Cortex 2.0 g, Zizyphi Fructus 2.0 g, Glycyrrhizae Radix 1.0 g, and Zingiberis Rhizoma 0.5 g. The Yukmijihwang-tang extract contains the following raw materials (on an adult dose per day basis, 6 g): Rehmanniae Radix 5.0 g, Cornus Fructus 3.0 g, Dioscoreae Rhizoma 3.0 g, Alismatis Rhizoma 3.0 g, Smilacis Rhizoma 3.0 g, and Moutan Cortex 3.0 g. Yukmijihwang-tang helps improve cognitive functions, self-organization, and social development [5, 12–15], and Yukgunza-tang improves gastrointestinal functions which facilitate food intake and promote growth in children [16, 17].

The medication doses are as follows: (1) for patients aged 12–47 months, a total dose of 4 g per day (Yukgunza-tang, e.g., 2 g, + Yukmijihwang-tang, e.g., 2 g), and (2) for patients aged 48–72 months, a total dose of 6 g per day (Yukgunza-tang, e.g., 3 g, + Yukmijihwang-tang, e.g., 3 g). The pediatric dose has been determined in accordance with the TKM pediatric science textbook. Patients will consume the herbal medicine with drinking water twice a day about 1 h after breakfast and lunch.

The researcher will check if the participant is taking the herbal medicine twice a day and will provide 2–3 days of herbal medicine at each visit. If the patient is unable to consume the herbal medicine, the duration of and reason for the discontinuation will be recorded on a separate chart. The researcher will check whether the stock and usage records of the herbal medicine match.

### Outcome measures

Assessment data will be collected at the study initiation and at 12 and 24 weeks thereafter (Table 2).

**Table 2 Tab2:** Overview of the outcome measures at different time points in the study

Study week	Screening	Baseline	1–11 wks	12 wks	13–23 wks	24 wks
Informed consent	●					
Inclusion/exclusion criteria	●					
Demographics	●					
Concomitant disorders	●					
Medical history	●					
Medication	●					
Adverse events/vital signs		●	●	●	●	●
**Assessment**						
Blood and urine test		●				●
Height/weight		●		●		●
GMFCS		●		●		●
GMFM-88		●		●		●
K-BSID III		●		●		●
GAS		●		●		●
PedsQL		●		●		●

*wks* weeks, *GMFCS* Gross Motor Function Classification System, *GMFM* Gross Motor Function Measure, *K-BSID III* Korean Bayley Scales of Infant Development III, *GAS* Goal Attainment Scale, *PedsQL* Pediatric Quality of Life Inventory

### Baseline assessments

The population statistics data include sex and age. The researcher will examine the patient’s height, weight, complex disease history, health problems, medication, rehabilitation status, and functional food intake. Blood and urine tests will be performed to check for liver- or kidney-related diseases. The blood test will include assessments for aspartate aminotransferase, alanine transaminase, total bilirubin, blood urea nitrogen, and creatinine. The urine test will include assessments of pH, protein and glucose levels, and occult blood. Prior to random selection, the patient’s GMFCS score will be evaluated by physical therapists who have completed the evaluation tool training.

### Primary outcome measurement

#### GMFM-88

The GMFM-88 is a standardized observational instrument to measure changes in gross motor function over time in children with CP. The GMFM-88 has five dimensions: A—lying and rolling (17 items); B—sitting (20 items); C—kneeling and crawling (14 items); D—standing (13 items); and E—walking, running, and jumping (24 items). The items are scored from 0 to 3 (0 = not starting, 1 = starting to move but performing within 10% of functional activity, 2 = performing from 10% to less than 100% of functional activity, 3 = performing functional activity perfectly). The GMFM-88 total score is calculated as the mean score of all five dimensions, and the goal total score is the mean of the scores for individual dimensions selected by assessors considering the GMFCS and age [18, 19]. In this study, changes in the total score and goal total scores at baseline, 12 weeks, and 24 weeks will be used as evaluation variables.

### Secondary outcome measures

#### GAS

The GAS developed by Kiresuk allows the establishment of appropriate and clear treatment goals and the measurement of treatment progress according to the individual goals [20]. Each goal is rated on a 5-point scale with the degree of attainment captured for each goal area: 0 = achievement of the expected level, 1 = better than expected outcome (somewhat better) or + 2 (much better), − 1 = worse than expected outcome (somewhat worse) or − 2 (much worse). GAS will be assessed by researchers.

#### K-BSID III

The K-BSID III is an individually administered instrument to measure the developmental functioning of infants and toddlers. It is appropriate for administration to children aged 1–42 months; hence, it will be used only for infants under the age of 42 months. The K-BSID III includes cognitive, language, motor, social-emotional, and adaptive behavior scales [21]. In this study, a licensed physical therapist who has undergone rigorous training in accordance with the recommendations in the K-BSID III guidelines will assess the participants in each area. Changes in the composite scores in each area at baseline and at 12 and 24 weeks will be used as evaluation variables.

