## Methods/design

### Patients

#### Inclusion criteria

Participants must meet the following conditions to be eligible: (1) aged 2–6 years and diagnosed with CP according to a combination of clinical findings and cerebral magnetic resonance imaging and (2) parental consent for participation in the study.

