**Fig. 2 Fig2:**
[figure not shown]
Standard Protocol Items: Recommendation for Interventional Trials (SPIRIT) schedule of enrollment, interventions, and assessments. GMFCS, Gross Motor Function Classification System; GMFM, Gross Motor Function Measure; K-BSID III, Korean Bayley Scales of Infant Development III; GAS, Goal Attainment Scale; PedsQL, Pediatric Quality of Life Inventory

The assessments will be performed three times in total: at baseline, 12 weeks (after 3 months), and 24 weeks (after 6 months). Two physical therapists with more than 5 years of experience in pediatric rehabilitation will evaluate the scores for each item and the recorded videos (the videos will be recorded by a physical therapist during assessment to evaluate the participants’ GMFM-88, GAS, and K-BSID III developmental status). In principle, the same person should conduct all three evaluations. Assessors will be blinded to the subject assignment, and an inter-rater reliability test will be conducted before each study. The proposed study protocol is schematically presented in Figs. 1 and 2.

Sample size calculations are based on a previous study [8]. We estimated a GMFM-88 score difference of 2.8 ± 3.2 (effect size, *d* = 0.8) which is considered to clinically indicate a change in motor function. A two-sided 5% significance level and 90% power were considered, and calculations indicated the requirement of approximately 28 participants in each group. Estimating a 30% dropout rate, each group will require 40 initial participants. Therefore, this study will be performed as a multicenter randomized controlled trial (RCT) by recruiting 80 subjects for a period of 2 years. Patients will be recruited from Pusan National University Hospital, Yangsan Pusan National University Hospital, Pusan Dongeui Hospital, and Bundang Cha Hospital.

In the event of a direct injury in relation to this study, appropriate medical action may be taken according to the decision of the clinical researcher. The level of compensation shall be an appropriate amount for the nature of the damage, its degree of consistency, and as would be generally decided by the courts in Korea and cover the entire treatment cost until the adverse event (AE) is cured. If rehabilitation therapy is required or an after-effect is noted, appropriate compensation will be provided after assessing the disorder.

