## Discussion

The aim of this trial is to investigate the efficacy and safety of IMR for children with CP in Korea. The results will help to demonstrate if IMR is an effective therapeutic approach for CP.

In a systematic review of the effects of acupuncture and herbal medicines in Chinese children with CP, six out of 35 RCTs reported AEs; however, these were not associated with acupuncture and herbal medicine treatment [6]. Despite the safety of acupuncture and herbal medicines, no large-scale RCTs have been conducted in Korea. This lack of evidence necessitates an additional RCT to evaluate the clinical efficacy of integrative medicine in patients with CP.

The acupuncture program includes body acupuncture and press needle acupuncture. The acupoints for body acupuncture include five head points (GV20, EX-HN1) and 12 limb points (bilateral LI4, LI11, LU9, ST36, LR3, and BL60). In cases of spastic CP, additional press needles will be used on the wrists and ankle joints (LI5, TE4, BL60, and KI4). A systematic review of literature in Korea and China has identified these acupoints to be effective for paralysis and cognitive impairment [10, 27, 28].

The herbal medicine to be used in this study is a combination of Yukgunza-tang extracts and Yukmijihwang-tang extracts. Yukmijihwang-tang extract has been reported to improve cognitive and motor function in experimental and clinical studies in children with CP [5, 12–15]. In contrast, Yukgunza-tang extracts have been used to improve the gastrointestinal function of children with CP, promote the absorption of Yukmijihwang-tang extract (K-13), and prevent digestive disorders as a result of Yukmijihwang-tang extract (K-13) administration [16, 17].

The primary outcome is the GMFM-88 score which assesses large motor function in CP. The secondary outcomes are the GAS, K-BSID III, and PedsQL™ scores and AEs. A limitation of this study is that UR is not fully controlled because this study is a pragmatic RCT. This study could potentially confirm whether integrative medicine is an effective rehabilitation therapy for CP. Our study may show that IMR is effective and safe for treating motor dysfunction, language disorder, and social-emotional disorders in children with CP.

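### K-BSID III is limited to children under 42 months, but its outcome is change to weeks 12 and 24, and no rule covers children who pass the limit in between

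*Protocol article*

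**What the plan says.** - **Eligibility** (Inclusion criteria): children "aged 2–6 years and diagnosed with CP".
- **Range of the scale** (K-BSID III section): "It is appropriate for administration to children aged 1–42 months", and therefore in this trial "it will be used only for infants under the age of 42 months".
- **Outcome** (same section): "Changes in the composite scores in each area at baseline and at 12 and 24 weeks will be used as evaluation variables".
- **Timing** (text under Fig. 2): assessments take place "at baseline, 12 weeks (after 3 months), and 24 weeks (after 6 months"). Table 2 schedules K-BSID III at all three visits and attaches no age condition.
- **Missing data** (Statistical analysis): last observation carried forward, with no exception for any outcome. The same section tests slopes from baseline to week 12 and from week 12 to week 24 for each outcome measure.
- **Expected conclusion** (Discussion): "Our study may show that IMR is effective and safe for treating motor dysfunction, language disorder, and social-emotional disorders in children with CP". The sentence has no age limit, and the limitation that the Discussion names is the uncontrolled usual rehabilitation, not the age range of this scale.

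**The concern.** The age limit and the outcome do not fit together. A change score needs the same child to be testable at both ends of the interval, and some children who qualify for the scale at baseline will have outgrown it by the later visit. The section does not say whether age counts at entry or at each assessment, and neither reading works as written.

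- **Limit at each visit.** The later score cannot be obtained, and the article's only missing-data rule fills the gap with an earlier score. The filled-in value then reflects the child's birth date, not development.
- **Limit at entry only.** No score is lost, but children are tested at ages above the range the article itself gives for the instrument.

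At stake is a named secondary outcome, and with it the social-emotional part of the expected conclusion. K-BSID III is the only outcome described with a social-emotional scale.

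**Working it through.** The article gives no number for the K-BSID III subset, so there is no stated figure to reproduce.

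**Inputs.** Upper limit 42 months (K-BSID III section); lowest entry age 24 months (Inclusion criteria); visits at 12 and 24 weeks; 80 children (sample size paragraph). The age distribution of recruits is not given.

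**Step 1: visit times in months** (30.4375 days per month).
- 12 weeks: 84 / 30.4375 = 2.76 months
- 24 weeks: 168 / 30.4375 = 5.52 months

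**Step 2: baseline age above which a child is out of range.** No distribution is needed here.
- By week 12: 42 − 2.76 = 39.2 months
- By week 24: 42 − 5.52 = 36.5 months

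With the article's own rounding to 3 and 6 months, the cut-offs are 39 and 36 months.

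**Step 3: share of starters who age out.** Assume ages are uniform from 24 months, so starters span 42 − 24 = 18 months.
- By week 12: 2.76 / 18 = 15%
- By week 24: 5.52 / 18 = 31%

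These shares do not depend on the upper entry age. They do depend on the lower one. The dosing bands and the age strata mention children from 12 months or 1 year, in conflict with the inclusion criterion. If ages were uniform from 12 months, the shares would be 2.76 / 30 = 9% and 5.52 / 30 = 18%.

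**Step 4: counts under the same assumption, before dropout.** The upper age is 72 months (the top dosing band reads "for patients aged 48–72 months") or 84 months if a child counts as six until the seventh birthday.

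| Upper age | Start the scale | In range at week 12 | In range at week 24 |
|---|---|---|---|
| 72 months | 80 × 18/48 = 30 | 80 × 15.24/48 = 25 | 80 × 12.48/48 = 21 |
| 84 months | 80 × 18/60 = 24 | 80 × 15.24/60 = 20 | 80 × 12.48/60 = 17 |

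**Step 5: what carry-forward does if the limit applies at each visit.**

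| Age at baseline | Last score in range | Value entered | Effect |
|---|---|---|---|
| About 39.2 to under 42 months | Baseline | Baseline score at weeks 12 and 24 | Zero change from baseline at both visits |
| About 36.5 to 39.2 months | Week 12 | Week-12 score at week 24 | Measured change to week 12; zero slope from week 12 to 24 |
| Under about 36.5 months | Week 24 | None | None |

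Under the uniform assumption the first row holds about 15% of starters and the second 31% − 15%, again about 15%.

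**The case against.** The strongest reply is that the restriction is openly stated, that it concerns a secondary outcome, and that a condensed article may leave the handling of age-outs to the full protocol or analysis plan. The Statistical analysis section also does not say that a test ruled out by age counts as a missing value. This has weight: it cannot be asserted that the plan will fill in values for these children. But the article does fix the age limit, the two change intervals and a carry-forward rule without exceptions. Taken together these leave one defect or the other, whichever reading applies, so this is more than an omitted detail.

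Four stronger readings are tempting, and the article does not support them.

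- A reader might infer that language is measured only by K-BSID III. The PedsQL section lists a speech and communication scale with no 42-month limit, scheduled at all three visits. Only the social-emotional statement depends on K-BSID III alone.
- A reader might infer that about a third of starters would receive zero change from baseline. Carry-forward uses the latest score, so that happens only to those out of range by week 12, about 15%. The 31% is everyone out of range by week 24, and about half of them would carry a measured week-12 score.
- A reader might take the week-24 share as the headline. The main comparison, stated for GMFM-88, runs from baseline to week 12, and by week 24 both groups have received the integrative treatment. The smaller share is the relevant one for the randomised comparison.
- A reader might infer that the K-BSID III analysis breaks a power commitment. No effect size or power is stated for it; the sample size assumption belongs to GMFM-88.

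**Conclusion.** The point holds as an internal conflict in a secondary outcome. The cut-off ages, about 39.2 months for week 12 and 36.5 months for week 24, follow from the article's own figures. The shares of 15% and 31% of starters, and the counts, rest on an assumed uniform age distribution and would shift with the real one.

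The consequence depends on which reading is meant: carried-forward values that are artefacts of age, or testing outside the stated range. The social-emotional part of the Discussion's expected conclusion is worded for children with CP in general, while its data would come from the youngest children only. The wording is hedged, but it carries no age limit. The primary outcome and the sample size are not affected.

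**What to change.** 1. In the K-BSID III section, analyse change to week 12 only in children under about 39 months at baseline, and change to week 24 only in those under about 36 months. These children stay in range: 39 + 2.76 = 41.8 months and 36 + 5.52 = 41.5 months.
2. In the Statistical analysis section, exclude children who pass 42 months from carry-forward on this scale.
3. In the Discussion, limit the social-emotional statement, and any language statement based on K-BSID III, to that age group. A language statement based on the PedsQL speech and communication scale need not be limited in this way.

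The cost is a few sentences and fewer K-BSID III values. Under the uniform assumption with entry up to 72 months, about 80 × 15/48 = 25 children would contribute to week 12 and 80 × 12/48 = 20 to week 24, before dropout, out of the 30 who start. With entry up to 84 months the figures are 80 × 15/60 = 20 and 80 × 12/60 = 16, out of 24.

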#### PedsQL™

The PedsQL™ Cerebral Palsy Module is a measurement model to measure health-related quality of life (HRQOL) in children with CP [22]. The PedsQL™ Cerebral Palsy Module includes daily activities, movement and balance, pain and hurt, fatigue, eating activities, school activities, and speech and communication. The score is rated on a 5-point scale (0 = never a problem; 1 = almost never a problem; 2 = sometimes a problem; 3 = often a problem; 4 = almost always a problem). Each item will be reverse-scored and linearly transformed to a 0–100 scale (0 = 100, 1 = 75, 2 = 50, 3 = 25, and 4 = 0). Higher scores indicate better HRQOL. In this study, the Korean version of the PedsQL™ 3.0 Cerebral Palsy Module questionnaire [23] will be used, and the changes in the scores at baseline and 12 and 24 weeks will be used as evaluation variables.

### Adverse events

Information regarding AEs will be collected through patient symptom reports and observations by researchers at each visit. The type of adverse reaction, severity, and causal relationship with the treatment will be determined and recorded in the case record. The severity of AEs will be assessed using Spilker’s three-step classification: 1 = mild (treatment is not needed, and the patient’s normal functioning is not significantly inhibited), 2 = moderate (the patient’s normal functioning is significantly inhibited), and 3 = severe (a high level of treatment is required, and the patient shows after-effects).

The AEs of acupuncture may include local inflammation, discomfort, sputum hemorrhage and bruising, pruritus, fever, and other acupuncture-related risks [24]. The AEs of herbal medicine may include indigestion, diarrhea, and urticaria [25]. To evaluate the safety of herbal medicine, blood and urine tests will be conducted for all participants at baseline and 24 weeks. In case of symptoms of drug-induced liver damage during the clinical study, liver function tests will be performed immediately after the discontinuation of herbal medicines with the assessment of drug-induced hepatitis using the drug-induced liver injury causality assessment scale [26].

### Statistical analysis

Researchers will analyze for our main objective by comparing the outcomes (GMFM-88) of children receiving UR with IMR (group A) and those receiving UR without acupuncture and herbal medicine (group B) between baseline and 12 weeks. Within-group comparisons for changes in the duration of IMR and UR will be performed. We will use linear mixed models to test group differences in improvements over time for each outcome measure while adjusting for the serial correlation introduced by repeated measurements on the same participants. Group assignment, GMFCS level, time, and their interactions were included as fixed effects, with age as a fixed-effect covariate; patient and patient-by-time effects were included as random effects. A heterogeneous autoregressive covariance structure will be used for the random effects. Rates of change (slopes) from baseline to 12 weeks and from 12 to 24 weeks will be tested to evaluate treatment effects. Rates of change from baseline to 24 weeks will be compared with overall improvement across outcomes. Missing values will be imputed using the last-observation-carried-forward method.

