### Study design

This is a multicenter pragmatic randomized controlled evaluator-blinded clinical trial of the effectiveness of IMR for CP. We will recruit participants by advertising on the Internet and through posters in hospitals and communities. The recruiting period will be from January 1, 2021, to December 31, 2022.

After explaining the “Guide for Study Subjects” to the participants’ guardian, their consent for clinical study participation will be obtained by the study investigators. The Guide for Study Subjects contains information on the effects of the study and adverse reactions as well as the safety data. The evaluations will be carried out after receipt of the consent forms. On the consent form, participants will be asked if they agree to the use of their data should they choose to withdraw from the trial. Participants will also be asked for permission for the research team to share relevant data with people from the Universities and hospitals taking part in the research. This trial does not involve collecting biological specimens for storage.

The participants will be randomly stratified into groups A and B. Randomization will be performed based on the Gross Motor Function Classification System (GMFCS) stage (stages 1–3 vs. stages 4–5), age (1–2 years vs. 4–6 years), and CP type (spastic vs. non-spastic). The principal researcher will use a block randomization method using a random block size to generate the random allocation sequence. Computer-assisted randomization will be performed using the Excel 2010 program, and the randomized sequences will be delivered in an opaque envelope to conceal allocation. After screening, the researcher will open the sealed envelope in the presence of the participant, and the assignment result will be confirmed.

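### The mixed model leaves out CP type and gives age only a main effect, so two of the three stratification factors do not adjust the 12-week contrast; the test stays unbiased but is slightly conservative

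*Protocol article*

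**What the plan says.** **Randomisation** (Study design). Three stratification factors are named. The first is GMFCS: "Randomization will be performed based on the Gross Motor Function Classification System (GMFCS) stage (stages 1–3 vs. stages 4–5". The other two are "age (1–2 years vs. 4–6 years), and CP type (spastic vs. non-spastic".

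**Model** (Statistical analysis). The fixed effects are "Group assignment, GMFCS level, time, and their interactions were included as fixed effects, with age as a fixed-effect covariate". For the random part, "patient and patient-by-time effects were included as random effects", and "A heterogeneous autoregressive covariance structure will be used for the random effects". CP type appears nowhere in the model, and no age-by-time term is named.

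**Contrast and missing data** (same section). The main objective compares the two groups on GMFM-88 between baseline and 12 weeks, and "Rates of change (slopes) from baseline to 12 weeks and from 12 to 24 weeks will be tested to evaluate treatment effects". Baseline is thus one of the modelled responses. "Missing values will be imputed using the last-observation-carried-forward method".

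The article does not say whether GMFCS enters as five levels or as the two randomisation strata, nor how the group effect is averaged over GMFCS.

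**The concern.** Stratification makes the groups alike on the chosen factors, which reduces the true sampling variation of the group difference. The analysis benefits only if the same factors are in the model in a form that acts on the contrast being tested. Otherwise the variance they explain stays in the residual, the reported standard error is too large, and the test rejects less often than its nominal level.

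Here CP type is missing altogether. Age is present, so a reader may believe it is adjusted for, but a term that shifts all three visits equally does not act on a change from baseline. At stake is some of the precision that the stratified design makes available, in a trial planned on 28 evaluable children per group.

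**Working it through.** **1. The plan's own figure.** Inputs from Study design: difference 2.8, SD 3.2, two-sided 5%, 90% power, 30% dropout.

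n = 2 × (1.960 + 1.2816)² × 3.2² / 2.8² = 2 × 10.507 × 1.306 = 27.4, so 28 per group; 28 / 0.7 = 40. Both agree with the article.

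At 28 per group, SE = 3.2 × √(2/28) = 0.855 and 2.8 / 0.855 = 3.274. Normal-approximation power is Φ(3.274 − 1.960) = 0.906; the t-based value is 0.895. The normal approximation is used below.

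**2. Why an age main effect does not adjust the contrast.** Rewrite each child's three values as baseline, change to week 12 and change to week 24. An age term with one coefficient for all visits appears only in the baseline equation and cancels from both changes. The change equations contain only group, GMFCS and their product. These are a subset of the baseline regressors, so generalised least squares on complete records gives the same change coefficients with or without age.

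A numerical check used one simulated complete three-visit data set, 28 per group and two GMFCS strata, with the covariance matrix held fixed. The group × week-12 coefficient (which in this coding refers to one GMFCS stratum) was:

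| Terms added | Estimate | SE, general covariance | SE, heterogeneous AR(1) |
|---|---|---|---|
| none | 8.036 | 2.824 | 1.207 |
| age main effect | 8.036 | 2.824 | 1.207 |
| age and CP type main effects | 8.036 | 2.824 | 1.207 |
| age × time | 8.601 | 2.857 | 1.221 |
| age × time and CP type × time | 8.566 | 2.859 | 1.222 |

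The group × GMFCS × week-12 coefficient was likewise −7.356 in the first three rows. The average over the two strata, 8.036 − 0.5 × 7.356 = 4.358, is therefore also unchanged. Adding CP type as a main effect alone would achieve nothing. Because the covariance was fixed, this table shows which terms act on the contrast; it does not show the precision gain.

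**3. Size of the loss.** Let R² be the share of variance in 12-week change explained by age and CP type together. It is not in the documents, so 0 to 0.20 is assumed. SD 3.2 is taken as the SD of change before adjusting for them, and the strata as balanced. With k = √(1 − R²), the true SE is 0.855 × k, while the model as written reports about 0.855. Then:

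- type I error as written = 2 × [1 − Φ(1.960 / k)]
- power as written = Φ((3.274 − 1.960) / k)
- power adjusted = Φ(3.274 / k − 1.960)

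| R² | k | Type I error as written | Power as written | Power adjusted | Gain, points |
|---|---|---|---|---|---|
| 0 | 1.000 | 0.050 | 0.906 | 0.906 | 0 |
| 0.05 | 0.975 | 0.044 | 0.911 | 0.919 | 0.8 |
| 0.10 | 0.949 | 0.039 | 0.917 | 0.932 | 1.5 |
| 0.20 | 0.894 | 0.028 | 0.929 | 0.956 | 2.6 |

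Simulation with stratified blocks, each factor explaining 5 to 10%, gave about 0.91 as written against 0.93 to 0.945 adjusted, with type I error 0.034 to 0.038 as written. A second stratified simulation at 10% each gave 0.917 against 0.947. Together these give a gain of roughly 0 to 4 points.

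**4. Averaging over GMFCS.** If the model contains group × GMFCS × time, an average with weights w over levels holding shares p has variance ratio Σ w²/p relative to the overall contrast. Weights equal to the shares give 1, so power stays at 0.906. Equal weights with a 70/30 split give 0.25 × (1/0.7 + 1/0.3) = 1.190 and Φ(3.274/√1.190 − 1.960) = 0.851. An assumed 40/20/10/15/15 split over five levels gives 1.233 and 0.838.

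**The case against.** The strongest reply is that nothing is broken. Omitting balanced stratification factors from a linear model causes no bias, type I error stays at or below 5%, and power as written remains about 0.91 or more on the plan's inputs. The variance shares are also assumptions, and at zero the gain is nil. All of this stands and limits the point to efficiency and consistency. It does not remove the mismatch: the article states its fixed effects, random effects and covariance structure, so this concerns a stated model and not a detail left to an unseen analysis plan.

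Three stronger readings are tempting, but the documents do not support them.

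- *Power falls below the 90% target.* Simulations give about 0.89 for the model as written only when allocation ignores age and CP type. The article stratifies on both.
- *The interaction with GMFCS reduces the treatment effect to one GMFCS level.* A reference-coded coefficient would have power of only 0.64 if its level held half the children and 0.31 if it held a fifth. But the article nowhere says the effect is read from such a coefficient, and its wording does not expressly list a three-way term. An average over levels keeps 0.84 to 0.91 in the splits shown. The interaction does not bias or shrink the effect.
- *CP type must be adjusted for because treatment differs by type* ("Patients with spastic CP will receive press needle treatment to reduce their muscle tone"). That is a reason to look at effect modification by CP type. It is not an argument for prognostic adjustment.

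**Conclusion.** The point holds as a minor one. Of the three stratification factors, only GMFCS adjusts the baseline-to-12-week contrast in the model as stated. The estimate is unbiased and the test conservative. With age and CP type jointly explaining 0 to 20% of the variance in 12-week change (an assumed range), actual type I error runs from about 0.05 down to 0.03, and adjustment adds about 0 to 4 percentage points of power at 28 per group.

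This rests on near-balanced strata, on the article's difference and SD, and on complete records, which LOCF produces. With incomplete records an age main effect could act slightly through the pattern of missingness. If the covariance is re-estimated, its standard error could also shift a little; neither amounts to real adjustment of the contrast.

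**What to change.** In the primary model keep group × time and GMFCS × time, and add age × time, CP type and CP type × time. The time interactions are essential; main effects alone would change nothing. Name one primary contrast: the group difference in change in GMFM-88 from baseline to week 12, averaged over GMFCS, with the weights stated. State whether GMFCS enters as five levels or as the two strata. Move any group × GMFCS × time term to a secondary effect-modification analysis.

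The cost is wording, settled before unblinding. The factors are known at randomisation, so no new data are needed. With three visits the additions use about five model degrees of freedom: two for age × time, one for CP type and two for CP type × time.
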